**INTRODUCTION**

Current lifestyle trends characterized by inactivity and poor dietary habits have led to a dramatic decline in the health of Canadians. In fact, among men and women aged 15-69, 47% have poor aerobic fitness and 60% are classified as overweight or obese (1,2). The health consequences of excess weight are well known and include among others, an increased risk for the development of cardiovascular disease and type 2 diabetes (3). A common precursor to these metabolic disorders is peripheral insulin resistance (4). While the metabolic causes of insulin resistance are widespread and complex, there is increasing evidence that physical inactivity could be the major initiating factor (5). On the contrary, regular exercise is an effective strategy to combat insulin resistance while also improving aerobic fitness, body composition and skeletal muscle metabolic health (3). Despite this knowledge and public health guidelines recommending that adults accumulate at least 150 minutes of moderate to vigorous intensity activity each week (3), 85% of Canadian’s do not meet these minimum physical activity guidelines (6). The potential to establish more practical time-efficient exercise strategies that improve skeletal muscle metabolic health and reduce the risk of chronic disease has enormous public health and health care spending implications.

Reasons for not engaging in regular exercise are numerous and complex, however a “lack of time” continues to be cited as a key barrier (7). Physical activity guidelines like those from Health Canada typically focus on a minimum number of minutes per week. An increasing body of evidence, however, suggests that intensity of exercise performed, and not necessarily the duration, is important when attempting to improve the health and fitness of the population. A recent 18 yr observational study which tracked activity patterns of over 5000 participants found that the relative intensity and not duration of cycling was related to all-cause mortality (8). Regardless of the cycling duration (even when under 30 min/wk), higher relative intensity was associated with much lower mortality rates. Similarly, Rosenkilde et al. (9) found that a group of overweight men who exercised for 30 min per day over 13 wks lost the same amount of fat mass as a group who trained 60 min per day. Based off of these findings, it appears that focusing on the duration of exercise may not be necessary for improving overall health. Perhaps developing short-duration, high-intensity exercise protocols would be an effective as well as appealing strategy to improve the fitness of the population.

High-intensity interval training, which consists of short bursts of intense exercise separated by periods of recovery, has repeatedly been shown to induce numerous performance, metabolic and health adaptations that resemble high-volume endurance training (10). Work from our laboratory over the past few years has specifically focused on a practical, time-efficient HIT model which consists of 10 x 1 minute cycle sprints at 90% maximal heart rate with 1 minute of recovery in between, totalling 20 min per session. We have shown that 2-6 weeks of low-volume HIT increases skeletal muscle mitochondrial capacity, glucose transporter (GLUT) 4 protein content and maximal oxygen uptake to the same extent as endurance training, despite a dramatically reduced time commitment associated with HIT (11,12). Additionally, this form of training has been shown to improve insulin sensitivity in previously sedentary adults (12) and glycemic control in patients with type 2 diabetes (13). We have also found 6 wk of HIT reduces fat mass and increases lean mass in overweight women ([name] et al., unpublished observations) which is consistent with findings from Trapp et al. suggesting 15 wk of low-volume HIT is superior to traditional endurance-type training for reducing total body mass and abdominal adiposity in young women (14). The 10 x 1min HIT protocol involves only 30 min of exercise within a 75 min time commitment per week including warm up and cool down, which equates to half that recommended by public health guidelines. This appears to highlight the efficacy of exercise intensity rather than duration in mediating physiological adaptations to training.

Two recent studies investigated the effect of extremely low-volume HIT models on markers of cardiorespiratory fitness and health. Metcalfe et al.(15) showed that as little as 2 20 s sprints during 10 min of low-intensity cycling 3x/wk improved VO_2_peak and insulin sensitivity (based on oral glucose tolerance tests) in young healthy males after only 2 wk. Similarly, Jakeman et al. (16) showed that 6 sessions of 10 x 6 s sprints with 1 min of recovery improved 10 km time trial performance. These preliminary studies are promising and appear to suggest that a 30 min time commitment per week could be sufficient to improve health and aerobic fitness if the exercise is performed at a high intensity. Additional studies are warranted with more comprehensive analyses including skeletal muscle adaptations to these very low-volume HIT protocols. Examining changes in skeletal muscle oxidative and substrate transport capacity, body composition and glycemic control in overweight individuals following 6 wk of very low-volume HIT will shed light on the value of exercise intensity in the face of a very low total time commitment. Therefore we aim to investigate the effectiveness of a HIT model requiring a 10 minute time commitment per day, 3 times per week, in an attempt to identify a practical and a time-efficient exercise strategy which can improve skeletal muscle metabolic capacity and glycemic control in overweight individuals.

**METHODS**

**Subjects**

Twenty men and women (n=10 each) between the ages of 18-45 years will be recruited through poster advertisement.

Inclusion criteria will include:

- Classification of “sedentary” based off a International Physical Activity Questionnaire (IPAQ) score of < 600 MET min/wk
- Body mass index (BMI) > 25/27 < 30kg/m

Exclusion criteria will include:

- Active cardiovascular disease
- Cerebrovascular disease including previous stroke or aneurysm (large vessel or intracranial
- Respiratory disease including pulmonary hypertension of COPD
- Metabolic disease including: parathyroidism, hyper/hypothyroidism, Cushing’s disease or type 1 or 2 diabetes
- Active inflammatory bowel disease
- Renal disease
- Malignancy
- Recent steroid treatment (within 6 mo), or hormone replacement therapy
- Clotting dysfunction
- Musculoskeletal or neurological disorders
- Any disease requiring long-term drug prescriptions, including statins

Details of the experimental protocol, purpose and potential risks of participation will be explained to all subjects and written informed consent will be obtained. Sample size is based on estimated changes in primary outcome variables and standard deviations obtained from analysis of previous studies. 8 subjects are required to detect changes at an alpha level of 0.05 with 80% power. To preserve power we will recruit 10 males and 10 females.

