**STATISTICAL ANALYSIS**

All data will be analyzed using a paired Student’s t-test with significance set at p ≤ 0.05.

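### Recruitment is fixed at 10 men and 10 women, but the only named test is a paired t-test with no sex term, and the 8 subjects are not said to be per sex or in total

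*Protocol*

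**What the plan says.** The Subjects section of the protocol holds the whole sample-size statement:

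- Source: "Sample size is based on estimated changes in primary outcome variables and standard deviations obtained from analysis of previous studies".
- Requirement: "8 subjects are required to detect changes at an alpha level of 0.05 with 80% power".
- Recruitment: "Twenty men and women (n=10 each) between the ages of 18-45 years will be recruited".
- Reason for recruiting more than 8: "To preserve power we will recruit 10 males and 10 females".

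No size of change, SD, sidedness or dropout rate is given, and the 8 is not labelled as a total or a per-sex number.

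The Statistical Analysis section is one sentence: "All data will be analyzed using a paired Student’s t-test with significance set at p ≤ 0.05". It does not mention sex, either as a factor or as a stratum. The aim at the end of the Introduction concerns a strategy "which can improve skeletal muscle metabolic capacity and glycemic control in overweight individuals", so it is stated for the whole group, with no comparison of men and women.

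**The concern.** Sex is a fixed feature of the design: a quota of 10 and 10, not whatever mix happens to volunteer. The named analysis makes no use of it. On its plain reading, one paired t-test on all data with one overall aim, the test takes its error from the spread of all 20 changes. If men and women respond differently, that spread includes the gap between the two sex means. The gap does not contribute to the sampling error of the mean change when the quota is fixed, so the interval is wider than it needs to be and some power is lost.

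The sample-size text adds to the difficulty. The step from 8 to 10 + 10 reads most naturally as 8 per sex with 2 spare, which points to tests within each sex. The Statistical Analysis section names no such tests. A reader cannot tell which analysis the 80% belongs to.

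**Working it through.** **Inputs.** From the protocol: 8 subjects, alpha 0.05, power 80%, recruitment 10 + 10, paired t-test. Assumed: a two-sided test, and the sex differences in response used in step 4. Throughout, d is the mean change divided by the SD of change (within sex, where the sexes differ).

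**1. The protocol's own figure.** With no change or SD stated, 8 cannot be derived forwards, so I solved backwards. Power = P(|T| > t(0.975, n−1)), where T is noncentral t with n−1 degrees of freedom and noncentrality d√n. For n = 8, 80% power needs d = 1.156 (noncentrality 1.156 × √8 = 3.27). One-sided, it needs d = 0.978. So 8 is a possible answer for the named test, if a large change is expected.

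**2. The two readings of 8.**
- Per sex: 8/(1 − 0.20) = 10, so 10 per sex leaves room for an assumed 20% dropout.
- In total: 20/8 = 2.5 times the requirement.

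| n | Power at d = 1.156 | d detectable with 80% power |
|---|---|---|
| 8 | 80.0% | 1.156 |
| 10 | 90.1% | 0.996 |
| 16 | 99.1% | 0.749 |
| 20 | 99.8% | 0.660 |

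The change for which the study has 80% power is therefore 1.156 SD or 0.660 SD, a ratio of 1.156/0.660 = 1.75, depending on whether the test uses 8 subjects or all 20.

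**3. What pooling does to the error term.** Let the sexes differ in mean change by δ (in within-sex SDs), with 10 of each. The mean of the 20 changes has variance σ²/20 whatever δ is. The pooled sample variance, however, has expectation σ²[1 + (20/19) × δ²/4].
- δ = 0.5: 1 + (20/19) × 0.0625 = 1.066, so the standard error is about √1.066 = 1.03 times too large.
- δ = 1: 1 + (20/19) × 0.25 = 1.263, so the standard error is about √1.263 = 1.12 times too large.

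**4. Effect on power and coverage.** Simulation with 20 completers, two-sided 0.05, one million runs per row:

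| Mean change (SD) | δ (SD, assumed) | Power, pooled | Power, sex fitted | Coverage of pooled 95% interval |
|---|---|---|---|---|
| 0.66 | 0 | 80% | 80% | 95.0% |
| 0.66 | 0.25 | 80% | 80% | 95.2% |
| 0.66 | 0.5 | 78% | 80% | 95.6% |
| 0.66 | 1 | 72–73% | 80% | 97.1% |
| 1.156 | 0 | 99.8% | 99.8% | 95.0% |
| 1.156 | 1 | 99.6% | 99.8% | 97.1% |

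The range 72–73% reflects the third decimal of the mean change (72.3% at 0.660, 72.5% at 0.662).

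**5. Price of fitting sex when it is not needed.** Error degrees of freedom fall from 19 to 18. With δ = 0 and d = 0.660, power goes from 80.0% to 79.8%, about 0.2 percentage points.

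**6. What 10 per sex can say about a sex difference.** By two-sample t power on the changes, a difference of 1.32 SD is detectable with 80% power. Power is 69% for a difference of 1.156 SD and 23% for half of that.

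**The case against.** The strongest case against the point has four parts.

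- **The sample size is sound for the named type of test.** This stands. A reader might infer that 8 matches no planned analysis, or that there is an arithmetic error. The protocol does not support that: 8 fits a paired t-test at about 1.16 SD, and 8 per sex plus 2 spare fits 10 + 10. On neither reading is the study underpowered at that change (90.1% at n = 10, 99.8% at n = 20). If 8 is the total, enrolling 20 exceeds the need and does preserve power.
- **Pooling is not stated.** This is correct. The Statistical Analysis section neither says that the sexes are pooled nor rules out tests by sex, and a separate analysis plan might settle it. Pooling is the plain reading of a single test on all data, but it remains an inference. What stays within the protocol is that it fixes the quota, the power claim and the test, and does not connect them.
- **No sex hypothesis exists.** This stands too. Recruiting both sexes does not oblige anyone to test for a difference. The case for a sex factor here is precision of the overall change, not a sex comparison.
- **The loss depends on the assumed gap.** This stands. It is under 2 points for differences up to 0.5 SD, and negligible at 1.16 SD. Only a large sex difference combined with a moderate mean change makes it matter.

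**Conclusion.** The point holds as a modest improvement in efficiency and clarity. The pooled paired t-test makes no use of the fixed sex quota, and its interval for the mean change is too wide whenever men and women respond differently. With 20 completers and a mean change of 0.66 SD, power drops from 80% to about 78% for a sex difference of 0.5 SD and to 72–73% for 1 SD. In the latter case the nominal 95% interval covers about 97%. These sex differences are assumptions, since the protocol gives no figure for them. The calculation also assumes a two-sided test and the pooled reading of the analysis. The test remains valid, because the error is on the conservative side.

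The unlabelled 8 is a gap in the sample-size statement, not a demonstrated mistake. The missing change and SD mean that it cannot be checked, but do not show it to be wrong.

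**What to change.** **Statistical Analysis section.** Analyse the change with sex as a between-subject factor, by a sex × time mixed model or the equivalent ANOVA. Take the time effect averaged over sex as the test. Report sex × time as an estimate with a 95% confidence interval only, and draw no conclusion of equal response from a non-significant result, because no sex hypothesis is stated and 10 per sex gives little power for one.

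**Subjects section.** State whether 8 is per sex or in total. Add that 20 completers give 80% power (two-sided 0.05) for a mean change of about 0.66 SD of the paired differences, or about 0.75 SD if 16 complete. The 16 is an assumed figure, as the protocol gives no dropout rate. Both values follow from the number of subjects alone and should not be presented as the expected change; that still has to come from the earlier studies on which the protocol relies.

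**Cost.** A few sentences and one model term. No extra participants or measurements are needed. The downside is one degree of freedom, about 0.2 percentage points of power if men and women respond alike.

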**Overview of Experimental Protocol**

This study consists of 4 phases: i) An initial screening visit; ii) Baseline Testing iii) 6wk of HIT; and iv) Post-training Testing; All phases are outlined below, with additional information on selected procedures following. Figure 1 at the end of the document depicts the experimental protocol.

**I) Initial Screening Visit**

Before subjects formally enter the study, they will be asked to report to the laboratory to ensure they are eligible for participation. During this visit (approximately 45 minutes), subjects will i) read and sign a consent form for the study; ii) conduct a health assessment (questionnaire, height, weight, resting heart rate and blood pressure); iv) provide a fasting blood sample obtained by venupuncture (8ml) and v) complete a physical activity questionnaire.

**II) Baseline Testing**

Once we determine that subjects have met our inclusion criteria, we will invite them to enter the baseline testing phase of the study. This period will include 4 visits to the laboratory: 1) Insertion of Continuous Glucose Monitor (CGM) and accelerometer (Actiheart) which will be worn for 72 hr; 2) DEXA and skeletal muscle biopsy; 3) A VO_2peak_ test; 4) HIT familiarization to become acquainted with the exercise protocol. Subjects will also be asked to complete at 3 d diet record.

**IV) Exercise Training (HIT)**

The exercise training will be 100% supervised and will consist of 3 sessions per week for 6 weeks. All sessions will begin with a 2 minute warm up followed by 6x20 second cycle sprints against 7.5% of their body weight interspersed with 1 minute of recovery. Heart rate and rating of perceived exertion will be monitored at each session. On the first training session participants will be asked to wear the CGM and Actiheart during exercise and for the following 48 hr to identify the acute effect of HIT on glycemic control.

**V) Post-training Testing**

24-48 hrs following the last training bout we will measure resting blood pressure and HR and insert the CGM and Actiheart which will be worn for the following 48 hr (time of interest will be 48-72 hr post training). 72 hr following the last training session participants will undergo a DEXA scan, skeletal muscle biopsy and fasting blood sample. We will also obtain the CGM and Actiheart at this time. At least 72 hr following the biopsy, participants will report to the laboratory for a VO_2peak_ test.

**PROCEDURES**

**Resting Blood Pressure and Heart Rate Measures**

An automated device will be used for measurement of resting HR and BP. Participants will be instructed to rest for 10 minutes prior to the measurement. HR and BP will be measured twice from the dominant arm while the subject is in supine position. This will occur at the initial screening visit and 24 hr post training.

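### Post-training resting BP and HR have two stated times and are the only post-training outcome that can be read before 48 h, so their change may include an effect of the last session

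*Protocol*

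**What the plan says.** The protocol times the post-training reading in two places. Procedures, Resting Blood Pressure and Heart Rate Measures: "This will occur at the initial screening visit and 24 hr post training". Methods, V) Post-training Testing: "24-48 hrs following the last training bout we will measure resting blood pressure and HR and insert the CGM and Actiheart". The second section adds that the devices stay on for 48 h and are collected at the 72 h visit.

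The only pre-training reading listed is the one in the health assessment at the initial screening visit. Of baseline testing the protocol says "This period will include 4 visits to the laboratory", and none of the four lists BP or HR. Position (supine) and rest (10 min) are fixed for both readings.

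On the effect of a single session, Methods, IV) Exercise Training asks participants at the first session to "wear the CGM and Actiheart during exercise and for the following 48 hr to identify the acute effect of HIT on glycemic control". For the post-training glucose data, V) Post-training Testing says "time of interest will be 48-72 hr post training". DEXA, biopsy and fasting blood are set at 72 h, and the VO2peak test at least 72 h after the biopsy.

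The Statistical Analysis section sends all data to a paired t-test at 0.05. There is one group and no control.

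**The concern.** There are two linked problems.

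First, the two sections can be followed differently. One reader would measure every participant at 24 h; another could measure some at 24 h and others at 48 h. Time since the last session would then vary between participants with no rule behind it.

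Second, under either wording the reading comes sooner after exercise than any other post-training outcome. The Continuous Glucose Monitoring section distinguishes the effect of one session from that of six weeks of training, and the post-training glucose window starts at 48 h. BP and HR have no such separation. The screening reading has no scheduled session before it, whereas the post-training reading follows a sprint session by 24 to 48 h. With no control group, whatever the last session leaves behind is counted as training effect in the paired comparison.

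**Working it through.** **Step 1: the two times.** 24 h (Procedures) against 24 to 48 h (Post-training Testing). The first lies at the lower end of the second, so they overlap but are not the same instruction.

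**Step 2: which time fits the schedule.** BP and HR are read at the visit where the devices go on. Inputs from V) Post-training Testing: 48 h of wear, collection at 72 h. End of wear = insertion time + 48; wear available by collection = 72 − insertion time.

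| Visit (h after last session) | 48 h of wear ends at | Wear if collected at 72 h |
|---|---|---|
| 24 | 72 h | 48 h |
| 36 | 84 h | 36 h |
| 48 | 96 h | 24 h |

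Only 24 h meets both the wear and the collection time. A visit at 48 h would still cover the 48 to 72 h window of interest, but not the stated 48 h of wear.

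**Step 3: BP and HR beside the other post-training outcomes.**

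| Outcome | Time after last session |
|---|---|
| Resting BP and HR | 24 h, or 24 to 48 h |
| Glucose, window of interest | 48 to 72 h |
| DEXA, biopsy, fasting blood | 72 h |
| VO2peak | at least 72 h after the biopsy |

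BP and HR alone can be read before 48 h. The 24 h reading lies inside the 48 h that IV) Exercise Training uses for the acute glycemic effect; the 24 to 48 h range lies inside it up to its limit.

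**Step 4: what a shift would do to the test (illustration only).** The documents give no carry-over figure for BP or HR, so the shift is an assumption. Let b be a shift unrelated to training, in SDs of the paired change, with no true training effect. The two-sided paired t-test then rejects with probability P(|T| > t(0.975, n − 1)), where T is noncentral t with n − 1 degrees of freedom and noncentrality b√n. For n = 20 and b = 0.3, the noncentrality is 0.3 × √20 = 1.34.

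| Assumed b | n = 20 | n = 10 |
|---|---|---|
| 0.1 | 7.1% | 5.9% |
| 0.2 | 13.6% | 8.8% |
| 0.3 | 24.7% | 13.6% |
| 0.5 | 56.5% | 29.3% |

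The nominal rate is 5%. The plan has no figure of its own to reproduce here: the stated requirement of 8 subjects comes without an effect size or SD and is not tied to BP or HR.

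**The case against.** The strongest reply is that the protocol sets no acute window for BP or HR. The 48 h belongs to the first session and serves "for the following 48 hr to identify the acute effect of HIT on glycemic control". The Continuous Glucose Monitoring section gives 72 h of monitoring around that session, so 48 h is not a firm limit even for glucose. This stands: carrying the window over to BP and HR is an analogy, and carry-over is plausible but not shown.

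A reader might also infer the following, which the documents do not support:

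- *The other outcomes were deliberately placed later to avoid the acute effect.* The protocol gives no reason for the 48 to 72 h or 72 h times.
- *Familiarity with the laboratory pushes BP and HR towards apparent benefit.* The contrast is there: a first visit against one after 18 supervised sessions (3 per week × 6 weeks). No section gives a direction or size for its effect.
- *The false-positive rate is several times nominal.* The rates in the working follow from whatever shift is assumed and would be the same for any outcome. At 0.1 SD they are close to 5%.
- *A screening-visit baseline is an error.* It is a choice, and fasting blood uses the same one.

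Two further replies have weight. The device arithmetic largely settles the contradiction in favour of 24 h. And BP and HR are absent both from the aim in the Introduction and from the outcomes named under Perspectives and Significance. Both lower the severity. Neither removes the need for one stated time, and the Statistical Analysis section still tests the change as it tests everything else.

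**Conclusion.** The point holds in a limited form. The mismatch between 24 h and 24 to 48 h is certain. It is also certain that BP and HR are the only post-training outcome that can be read before 48 h, and that their change is tested without a control group. That the change mixes a last-session effect with the training effect is a possibility resting on analogy with the glucose window. Its size and direction are unknown from the documents, and the rejection rates in the working are conditional illustrations, not estimates for this trial. Because BP and HR are outside the stated aim, the trial's main conclusions are not affected. Severity is minor to moderate and confidence moderate; the change is worth making because it is nearly free.

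**What to change.** 1. State one time for the post-training BP and HR reading, the same in Procedures and in V) Post-training Testing. Take it at the planned 72 h visit, supine after 10 min of rest, before blood draw and biopsy. This aligns it with DEXA, biopsy and fasting blood, and matches the fasted state of the screening visit, since the Fasting Blood Sample section sets a 10 h fast for both.
2. Reconcile the device-insertion time with the 48 h of wear and collection at 72 h. Moving the BP and HR reading does not settle that by itself.
3. Optionally, add a pre-training reading under the same conditions (fasted, before procedures) at a planned baseline visit. In the listed order, the first two visits come before the VO2peak test and the familiarization session. No fast is stated for any of the four visits, so it would have to be added. This reduces the first-visit difference but does not remove it.
4. Report the BP and HR change as exploratory and uncontrolled.

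Cost: one assessment moved between visits already planned and, if the option is used, about 10 to 15 minutes with an automated device at one existing visit.

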**Fasting Blood Sample**

Following a 10 hr overnight fast on the initial screening visit and 72 hr post training, we will obtain a fasting plasma and serum sample by venupuncture (8ml).

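### Food intake and time of day are not matched between the two resting HR/BP readings: baseline falls at a fasting visit, the post-training reading at a visit with no prescribed fast

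*Protocol*

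**What the plan says.** **Baseline reading.** Under I) Initial Screening Visit, the visit of about 45 minutes includes, as item ii, "conduct a health assessment (questionnaire, height, weight, resting heart rate and blood pressure". Item iv of the same visit is to "provide a fasting blood sample obtained by venupuncture (8ml". The Fasting Blood Sample section sets the condition: "Following a 10 hr overnight fast on the initial screening visit and 72 hr post training, we will obtain a fasting plasma and serum sample".

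**Post-training reading.** Under V) Post-training Testing: "24-48 hrs following the last training bout we will measure resting blood pressure and HR and insert the CGM and Actiheart". The fasting blood comes at a different visit: "72 hr following the last training session participants will undergo a DEXA scan, skeletal muscle biopsy and fasting blood sample".

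**Conditions of the reading.** The section on Resting Blood Pressure and Heart Rate Measures asks for an automated device, two readings, the dominant arm and a supine position, and adds "Participants will be instructed to rest for 10 minutes prior to the measurement". It gives the timing as "This will occur at the initial screening visit and 24 hr post training". Neither food intake nor clock time is mentioned.

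**Analysis.** The Statistical Analysis section applies a paired t-test to all data at the 0.05 level. No control group is described.

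**The concern.** The plan imposes a fast on the visit that holds the pre-training reading and none on the visit that holds the post-training reading. Following it as written pairs a fasted reading with one whose prandial state is left open. Resting HR and BP may differ between the two states for reasons unrelated to six weeks of training.

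In a single-group design, any consistent difference in measurement conditions goes wholly into the estimated change. It could hide a real training effect or produce an apparent one. No analysis plan can restore the match afterwards, because the conditions are set when the reading is taken.

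**Working it through.** **Step 1. The two readings side by side.**

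| | Baseline | Post-training |
|---|---|---|
| Visit | Initial screening | Insertion of CGM and Actiheart |
| Timing | Before entry | 24 hr (Procedures) or 24-48 hr (V) Post-training Testing) after the last bout |
| Fast prescribed at that visit | 10 hr overnight, for the blood sample | None |
| Clock time | Not stated; morning is likely after an overnight fast | Not stated; at exactly 24 hr it is the hour of the last session |
| Rest, arm, posture, number of readings | Fixed | Fixed, the same |

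At screening, HR/BP is listed before the blood draw within one short visit. A participant who keeps to the fast is therefore fasted when HR/BP is read. This is a strong inference from the content and order of the visit; the Protocol does not state it as a condition of the HR/BP reading.

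**Step 2. Does the standardised diet close the gap?** No. The Continuous Glucose Monitoring section ties that diet to the monitoring period. After training, this period starts at the visit where HR/BP is read, so intake before the reading is not covered.

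**Step 3. Does the 24 hr timing fix the clock time?** It ties the reading to the hour of the last training session, not to the hour of the screening reading. The two agree only if the last session happens to be at that hour.

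**Step 4. What could a mismatch do? (illustration only)** The Protocol gives no SD, expected change or prandial shift for HR or BP, so there is no figure of its own to reproduce here. I therefore express an assumed consistent shift *b* and a true change *d* in units of the SD of the pre-post change. I take a two-sided paired t-test at 0.05 with all 20 recruited participants analysed together:

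- rejection probability = P(|T| > t(0.975, n−1)), where T is noncentral t with n−1 df and noncentrality √n × (net standardised change);
- n = 20 gives 19 df and a critical value of 2.093.

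For the no-effect column the net change is *b*. For the masking column it is 0.66 − *b*, because *d* = 0.66 has 80% power at n = 20. For example, *b* = 0.25 gives noncentrality √20 × 0.25 = 1.118 and a rejection rate of 18.6%.

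| Assumed shift *b* (SD of change) | Rejection rate, no true effect | Power for *d* = 0.66, shift opposing |
|---|---|---|
| 0 | 5.0% | 80% |
| 0.10 | 7.1% | 66% |
| 0.25 | 18.6% | 41% |
| 0.50 | 56.5% | 10.5% |

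In heart-rate units, again purely assumed, take a true fall of 4 bpm and a change SD of 6 bpm. Then *d* = 4/6 = 0.667 and power is 81%. An opposing mean shift of 1 bpm leaves (4−1)/6 = 0.50 and about 56% power; 2 bpm leaves (4−2)/6 = 0.333 and 29%. Over SDs of 5 to 8 bpm, power runs from 92% down to 56% with no shift, and from 40% down to 19% with a 2 bpm shift.

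**The case against.** A reader might infer that the post-training reading is taken in the fed state, so that a fed-versus-fasted bias is certain. The Protocol does not support this. It is silent on food at that visit, and participants may arrive fasted, fed or mixed. A bias can enter, but the text does not show that it does. Nor does the text give a direction: that a recent meal would raise resting HR and so mask a fall is an outside assumption, and for BP not even that much is on offer.

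Three further objections carry weight:

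- **Importance.** The aim at the end of the Introduction and the list under Perspectives and Significance concern muscle metabolism, glycaemic control and body composition. Neither names resting HR or BP, and HR/BP is not identified as a primary outcome. The rule that all data are tested brings HR/BP into the analysis, but no stated aim rests on it.
- **Magnitude.** Every effect, SD and shift in Step 4 is assumed. That power vanishes once the shift equals the effect is true by construction.
- **Timing.** It would be too much to say that the post-training reading may fall at any hour, since one section fixes it at 24 hr after training. Matching the screening clock time has to be squared with that.

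All of these stand, and they limit the point to a minor one. They do not remove it. The unequal fasting requirement is in the Protocol's own visit schedule, and the detailed conditions for the reading leave out the one item on which the two visits differ by design.

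**Conclusion.** The point holds in a limited form. The resting HR/BP comparison pairs a reading at a fasting visit with one at a visit where no fast is prescribed and the time of day is not matched, so the two may not be comparable. With one group and a paired t-test, any consistent difference would be counted as a training effect.

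The size and direction are unknown. The figures in Step 4 show only that a consistent shift of a quarter to half an SD of the change would matter, assuming 20 complete pairs and a two-sided test. The stated aims on muscle, glycaemic control and body composition are not affected. This is a minor, cheap improvement.

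**What to change.** In V) Post-training Testing and in Resting Blood Pressure and Heart Rate Measures:

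1. Require the post-training HR/BP reading to follow the same 10 hr overnight fast as the screening visit, at about the same time of day as the screening reading.
2. State that the reading is taken before CGM insertion, which is already the order in which the steps are listed.
3. Reconcile the 24 hr and 24-48 hr timings so that the matched clock time is feasible. A fixed 24 hr allows it only if the last session is at the screening hour; a 24 hr wide window contains every clock hour.
4. Record the time of the last meal and the clock time at both readings, so that departures can be seen.

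As a cross-check, report the Actiheart heart rate already recorded before and after training, for example overnight. This covers HR but not BP.

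**Cost.** Participants attend one more morning visit fasted; no new visit, device or staff is needed. If the visit is moved later in the 24-48 hr window, CGM wear before the 72 hr visit shortens from 72 − 24 = 48 hr towards 72 − 48 = 24 hr. The 48-72 hr period of interest is still covered, but the stated 48 hr of wear should be reconciled at the same time.
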